## Abstract

**Background:**

Postmenopausal osteoporosis (PMOP) and knee osteoarthritis (KOA) are common musculoskeletal disorders that share risk factors such as aging, hormonal changes, and inflammation. PMOP often remains asymptomatic until fractures occur, while KOA leads to pain and disability. Their comorbidity remains underexplored, particularly in community settings. This study aims to investigate the prevalence, risk factors, and clinical features of PMOP-KOA comorbidity among Beijing residents aged 45–80 years, providing evidence-based recommendations for early identification, prevention, and management.

**Methods:**

Over 2 years, this study will conduct a PMOP-KOA screening and prospective follow-up in the Beijing community to investigate the incidence, risk factors, and clinical characteristics of PMOP-KOA. This study will undertake bone mineral density detection, collect biological samples, and record information via questionnaires.

**Discussion:**

The study aims to investigate the incidence, risk factors, and clinical characteristics of PMOP-KOA comorbidity and explore related traditional Chinese medicine syndromes based on large community-based samples in Beijing. Data on PMOP-KOA occurrence and associated risk factors over the 2 years follow-up will be available on the Chinese Clinical Trial Registry (ChiCTR2300073575).

## 1 Introduction

Postmenopausal osteoporosis (PMOP) and knee osteoarthritis (KOA) are common age-related degenerative musculoskeletal disorders. As society has aged, they have become significant health concerns, particularly for postmenopausal women, affecting both physical and mental wellbeing (1). PMOP and KOA share similar pathological mechanisms, including abnormal bone metabolism in subchondral bone and age-related changes (2, 3). The comorbidity of KOA and PMOP may have interconnected effects on bone mineral density (BMD) and bone metabolism, with KOA patients typically exhibiting increased systemic BMD, while PMOP patients experience decreased BMD (4). This opposing trend in BMD changes may be attributed to KOA’s influence on bone formation and PMOP’s promotion of bone resorption, highlighting the metabolic heterogeneity in PMOP-KOA patients. The complexity of bone metabolism changes in these two conditions, along with the lack of clear early diagnostic biomarkers, remains a major challenge, making the clinical management of comorbidity more difficult.

In recent years, an increasing number of countries have started to be more concerned about community-based public health programs (5–7). Typically, there is a large population with KOA or PMOP in the community, which are undiagnosed before fractures occur, meaning that community-based health programs for PMOP and KOA screening could be of great significance to residents. Studies have shown that most KOA patients also suffer from osteoporosis, with approximately one in five osteoporosis patients concurrently diagnosed with osteoarthritis (8, 9). However, epidemiological findings on PMOP, KOA, and other potential influencing factors vary across different regions (10). Additionally, a lack of follow-up is common in the majority of community-based studies.

This prospective study will investigate conventional risk factors and relevant symptoms as reported in traditional Chinese medicine in populations with a high risk of PMOP (11, 12). Based on the findings of this preliminary research, we will then conduct a further cross-sectional survey and a prospective follow-up study in the Beijing community. This prospective study aims to investigate the prevalence of PMOP and KOA, explore associated risk factors, and provide evidence-based recommendations for their prevention and management. Additionally, the study will conduct transcriptomic analyses on samples from different subtypes of PMOP-KOA patients to identify differentially expressed genes (DEGs) with high specificity and sensitivity. These DEGs will serve as potential biomarkers for PMOP-KOA subtyping, offering valuable molecular insights into disease classification and paving the way for personalized treatment strategies. This research on “Beijing Community Postmenopausal Osteoporosis and Knee Osteoarthritis Screening: a cross-sectional and prospective Study (BEYOND)” will provide reliable data for the prevention of PMOP-KOA among community-dwelling residents in Beijing area.

## 2 Materials and methods

This is a community-based cross-sectional and prospective follow-up study. Through a preliminary literature review of both Chinese and English databases, we found that research on PMOP-KOA remains unstandardized, lacking support from multicenter, large-sample epidemiological studies. There is still a gap in understanding the clinical characteristics of patients with both conditions, as well as the genetic differences among PMOP-KOA patients with distinct traditional Chinese medicine (TCM) syndrome classifications. To address these gaps, we will recruit residents from 12 communities, applying predefined inclusion and exclusion criteria to screen participants for an epidemiological investigation. Data collection will include bone mineral density measurements, biological samples, and questionnaire-based information. Each participant will be followed for at least 2 years to track disease progression in PMOP-KOA patients. A flowchart of the research process is shown in Figure 1.

**FIGURE 1 F1:**
[figure not shown]
Study flow.

### 2.1 Participant recruitment

Due to the significant geographic and socioeconomic variations across different communities in Beijing, and considering the potential impact of economic status on bone mineral density, this study will recruit participants from Chaoyang District and Fengtai District. This approach aims to minimize potential biases related to educational background, work environment, and economic conditions.

Within these two administrative districts, 3–5 communities will be randomly selected. Local committees representing community residents or healthcare services will then be contacted. We will collaborate with community staff to post recruitment advertisements in public spaces, outlining the study’s objectives, content, significance, and potential benefits for participants.

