### 2.4 Inclusion and exclusion criteria

The inclusion criteria for this study are as follows: (1) Participants must have resided locally for more than 10 years; (2) Participants must meet the diagnostic criteria for KOA, with a KL grade of II or higher (unilateral or bilateral), and simultaneously fulfill the diagnostic criteria outlined in the Guidelines for the Diagnosis and Treatment of Primary Osteoporosis for comorbid osteoporosis; (3) Participants must be postmenopausal women aged 50–65 years (50 ≤ age < 65); (4) Participants must not have taken estrogen or medications affecting bone metabolism (e.g., glucocorticoids, antiepileptic drugs, aluminum-containing antacids, proton pump inhibitors, chemotherapy drugs, anticoagulants, or thiazolidinediones) within the past month; (5) Participants must voluntarily enroll in the study, sign an informed consent form, and ensure that the consent process fully adheres to ethical principles.

The exclusion criteria are as follows: (1) Participants with physical disabilities that severely limit mobility or the ability to comply with study procedures, as assessed by clinical investigators; (2) Participants with other autoimmune diseases; (3) Participants with serious heart, liver, or kidney comorbidities; (4) Participants who are pregnant or lactating; (5) Participants who have received immunosuppressive therapy within the last 3 months; (6) Participants who are unwilling or unable to complete follow-up.

To minimize recall bias in fracture reporting, all self-reported fracture events must be confirmed through radiographic evidence (X-ray or CT report); cases without objective imaging confirmation will be excluded from fracture-related analysis.

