### 2.5 Sample size

Through multiple clinical pilot investigations and expert consultations, a standardized participant information collection form has been developed and refined. Additionally, based on a comprehensive review of prior literature and expert discussions, this study has preliminarily identified the characteristic clinical symptoms and physical signs of PMOP-KOA. To estimate the required sample size, the Kendall method was initially applied, multiplying the number of variables by five, yielding a minimum sample size of 150 participants (15). To further enhance methodological rigor, a supplementary power analysis was conducted. Assuming a medium effect size (Cohen’s d = 0.5), a significance level (α) of 0.05, and a power (1–β) of 0.80, the required sample size for detecting group differences was calculated to be approximately 128 participants using standard formulas. Allowing for a 15% attrition rate due to potential loss to follow-up or incomplete data, the final target sample size was set at 150 participants. This dual approach ensures both practical feasibility and statistical robustness.

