### 2.11 Data management and statistical analysis

Data entry and logical verification were performed by two independent personnel using an electronic management system (National Copyright Registration Number: 2023SR0693141) to handle missing and abnormal values, ensuring data accuracy. Quality control measures were established in accordance with the requirements of clinical epidemiological cross-sectional studies and the specific characteristics of TCM research (21, 22). For standardization, all knee X-ray imaging and BMD assessments for participants from all community sub-centers were conducted at Beijing Electric Power Hospital. All recorded data must be preserved as original records and must not be altered arbitrarily.

Statistical analysis was performed using R 4.3.1. Continuous variables are presented as mean ± standard deviation ($\bar{\text{x}}$ ± s), while categorical variables are reported as percentages. Fisher’s exact test or Chi-square test was used for between-group comparisons. Variance estimation was performed using Taylor series linearization and replication methods. A two-sided *P*-value < 0.05 was considered statistically significant.

To control for potential confounding variables—such as body mass index (BMI), physical activity, dietary habits, and history of estrogen treatment multivariable regression models (e.g., logistic regression or Cox proportional hazards models for time-to-event data) will be employed. In addition, propensity score matching (PSM) or inverse probability of treatment weighting may be used where appropriate to balance covariates among comparison groups and enhance causal inference validity.

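### The plan gives two irreconcilable numbers of communities (12 and 3–5), and its survey variance method depends on that number and on a probability sample that recruitment by advertisement does not supply

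*Protocol article*

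**What the plan says.** Four statements in the protocol article bear on this point.

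- Section 2 (Materials and methods), on the size of the first sampling stage: "we will recruit residents from 12 communities".
- Section 2.1 (Participant recruitment), on the same stage: "this study will recruit participants from Chaoyang District and Fengtai District", and then "Within these two administrative districts, 3–5 communities will be randomly selected". It does not say whether 3–5 is a total or a number per district.
- Section 2.1, on how individuals are reached once communities are chosen: "We will collaborate with community staff to post recruitment advertisements in public spaces". Section 2.4 adds: "Participants must voluntarily enroll in the study, sign an informed consent form".
- Section 2.11, on variance: "Variance estimation was performed using Taylor series linearization and replication methods".

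Prevalence of the comorbidity is a stated aim in the Abstract, the Introduction and the Discussion.

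**The concern.** The number of communities is an operative design figure, and the plan fixes it at two incompatible values. It matters beyond tidiness. Taylor linearization and replication estimate variance from the spread between first-stage units, so the number of those units decides how well the variance is known and how wide an honest interval must be.

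The same methods take their meaning from a sample drawn with known selection probabilities. Here the random draw stops at the community, and individuals then come forward themselves. An interval from a survey procedure would look like a statement about the residents of these communities. The sampling described supports only a statement about those who volunteered.

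**Working it through.** **1. The plan's own sample size.** Section 2.5 states: "Assuming a medium effect size (Cohen’s d = 0.5), a significance level (α) of 0.05, and a power (1–β) of 0.80". Section 2.11 makes the test two-sided: "A two-sided *P*-value < 0.05 was considered statistically significant".

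- Normal approximation: n per group = 2 × (1.960 + 0.842)² / 0.5² = 62.8, so 63 per group and 126 in total.
- With the t distribution: 63.8, so 64 per group and 128 in total, which is the plan's figure.
- Attrition of 15%: 128 / 0.85 = 150.6 (151), or 128 × 1.15 = 147.2 (148). The stated 150 lies between these.

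The figures reproduce. They contain no term for clustering, and the point made here does not depend on them.

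**2. Can 12 and 3–5 be reconciled?**

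- As a total: 3, 4 or 5. Not 12.
- Per district, two districts: 2 × 3 = 6 up to 2 × 5 = 10. Not 12.
- For 12 communities in two districts, the average would have to be 12 / 2 = 6 per district, outside 3–5.

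**3. What the number does to the variance.** Assumption: community is the primary sampling unit, since it is the only unit said to be randomly drawn. Design df = communities − strata. The plan names no strata, so both cases are shown.

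| Communities | df, no strata | t(0.975) | df, districts as strata | t(0.975) |
|---|---|---|---|---|
| 3 | 2 | 4.30 | not estimable: split 2+1 leaves one district with a single community | – |
| 4 | 3 | 3.18 | 2 (if 2+2) | 4.30 |
| 5 | 4 | 2.78 | 3 (if 3+2) | 3.18 |
| 6 | 5 | 2.57 | 4 | 2.78 |
| 10 | 9 | 2.26 | 8 | 2.31 |
| 12 | 11 | 2.20 | 10 | 2.23 |

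With districts as strata, a 3+1 or 4+1 split also leaves one district without an estimable variance.

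For the same standard error and no strata, an interval from 3–5 communities is 2.78 / 2.20 = 1.26 to 4.30 / 2.20 = 1.95 times as wide as one from 12. The variance estimate is also less stable. Its approximate relative standard error, √(2/df), is 1.00 to 0.71 at 2–4 df, against 0.43 at 11 df.

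**4. Is there a probability sample?**

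- Stage 1, communities: described as randomly selected.
- Stage 2, individuals: advertisement and voluntary enrolment. No sampling frame, selection probability or weight is described.

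The first stage can support a between-community variance. The second gives no basis for inference from respondents to all residents.

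**The case against.** The strongest reply is that a journal article condenses the protocol. Sampling unit, strata, weights and rules for degrees of freedom commonly sit in the full protocol or the analysis plan, and their absence here is no finding. That is right, and none of those absences is charged. Condensing does not explain two different numbers for one sampling stage, or a survey variance method set beside recruitment by advertisement.

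Several stronger readings are tempting, and the document does not support them.

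- *The variance method fails at 3–5 communities.* Strictly, it breaks down only where a stratum holds one community. That is unavoidable only with 3 in total and districts as strata, and the plan does not call districts strata. Otherwise it runs but is very imprecise if 3–5 is the total. At 3–5 per district it has 4–8 df with strata and is usable.
- *The multiplier for 3 communities is 12.7.* That is the t value for a nominal 1 df (3 − 2). In that configuration one district's variance cannot be estimated, so no multiplier is correct.
- *Intervals will be far too narrow because 1.96 is used.* The plan states no critical value for intervals. If 1.96 were used at 2–4 df, coverage would be about 81–88%, but that is conditional on a choice that the plan does not state.
- *A design effect on 150 women shows the loss for prevalence.* Section 2.4 requires every enrolled woman to have both conditions, so prevalence among the 150 is 100% by construction. A prevalence needs the screened population as denominator.
- *Volunteers over-represent knee pain, and weighting by age and sex would repair it.* The first is plausible but not documented. The second would not remove selection on symptoms, and sex is moot because only women are eligible.

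The limitations paragraph in the Discussion concedes limited generalizability because recruitment is confined to particular Beijing communities. It does not mention self-selection within them.

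**Conclusion.** The concern holds in this form. The contradiction rests on the text alone and stands under either reading of section 2.1. Its consequence rests on one labelled assumption, that community is the sampling unit: 2–4 df if 3–5 is an unstratified total, fewer or not estimable if districts are strata, and 10–11 df with 12. The mismatch between survey variance and volunteer recruitment also follows from what the plan states. A survey interval may describe variation between communities among volunteers, but it cannot be presented as covering a community prevalence. The size of any self-selection bias cannot be derived from the document. This should be corrected before analysis; it does not invalidate the study.

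**What to change.** 1. State one number of communities in sections 2 and 2.1, and say whether it is per district.
2. In section 2.11, name community as the cluster, say whether districts are strata, and use t intervals with the design degrees of freedom (communities minus strata).
3. If only 3–5 communities in total are used, delete the Taylor and replication sentence and handle community in the model, for example as a fixed effect. This costs 2–4 parameters and makes inference conditional on the communities studied.
4. Label estimates as proportions among screened volunteers, with the number screened as denominator. Claim community prevalence only if a probability sampling step within communities is described.

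The cost is mainly wording. The price is wider intervals and a more modest prevalence claim.

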### 2.2 Ethics and registration

This study has received approval from the Medical Ethics Committee of Wangjing Hospital, China Academy of Chinese Medical Sciences (Approval No.: WJEC-KT-2023-010-P002) and has been registered with the Chinese Clinical Trial Registry (Registration No.: ChiCTR2300073575). Prior to participation, all individuals or their legal representatives will be fully informed about the study and required to sign an informed consent form, adhering to the principles of the Helsinki Declaration.

### 2.3 Diagnostic criteria

According to the World Health Organization (WHO) and the Chinese Guidelines for the Diagnosis and Treatment of Primary Osteoporosis (13), the diagnosis of OP is primarily based on BMD measurements using dual-energy X-ray absorptiometry (DXA). The diagnostic criterion for OP, based on DXA measurements of axial bones (lumbar spine L1-L4, femoral neck, or total hip) or the distal one-third of the radius, is a T-score ≤ −2.5. According to the Chinese Guidelines for the Diagnosis and Treatment of KOA (14), the diagnostic and KL grading criteria for KOA are detailed in Table 1.

**TABLE 1 T1:** Diagnostic criteria.

**OP**	
T-score ≥ −1.0	Normal
−2.5 < T-score < −1.0	Low bone mass
T-score ≤ −2.5	Osteoporosis
T-score ≤ −2.5 + Fragility fracture	Severe osteoporosis
**KOA**	
① Recurrent knee joint pain within the past month	KOA diagnosis: satisfies criterion 1+ any 2 of criteria 2, 3, 4, or 5.
② X-ray (standing position or weight-bearing position) shows joint space narrowing, subchondral bone sclerosis, and/or cystic changes, with osteophyte formation at joint margins	
③ Age ≥ 50 years	
④ Morning stiffness lasting ≤ 30 min	
⑤ Presence of crepitus during movement	
**Kellgren & Lawrence (KL) grading**	
No changes (normal)	0
Joint space appears normal (doubtful osteoarthritis)	I
Possible joint space narrowing (mild osteoarthritis)	II
Definite joint space narrowing with sclerosis (moderate osteoarthritis)	III
Severe joint space narrowing with significant sclerosis and bone deformities (severe osteoarthritis)	IV

Traditional Chinese medicine syndromes represent specific stages in KOA or PMOP progression, influenced by both internal and external factors. TCM-based treatment considers an individual’s constitution, environmental conditions, and seasonal changes, following the principle of “treatment based on syndrome differentiation.” This approach is fundamental in TCM, involving the identification of syndromes through symptom analysis and physical examination methods such as inspection, auscultation, olfaction, and palpation. By classifying patients based on syndrome differentiation, TCM provides a framework for stratifying individuals and selecting appropriate treatments tailored to distinct clinical presentations.

According to the Guidelines for the Diagnosis and Treatment of Osteoarthritis (2018 edition) and the Guidelines for the Diagnosis and Treatment of Primary Osteoporosis (2022 edition) issued by the China Association of Chinese Medicine, the primary TCM syndromes commonly observed in patients with KOA and PMOP include yang deficiency, yin deficiency, and combined yin-yang deficiency. In this study, syndrome classification will be conducted by two independent TCM practitioners with senior titles based on a standardized TCM four-diagnostic information collection form (inspection, listening/smelling, inquiry, palpation). In cases of disagreement, a third senior practitioner will be consulted for arbitration. Inter-rater reliability will be assessed using Cohen’s kappa coefficient to ensure diagnostic consistency. Participants will then be classified accordingly, and peripheral blood samples will be collected for high-throughput sequencing analysis.

### 2.4 Inclusion and exclusion criteria

The inclusion criteria for this study are as follows: (1) Participants must have resided locally for more than 10 years; (2) Participants must meet the diagnostic criteria for KOA, with a KL grade of II or higher (unilateral or bilateral), and simultaneously fulfill the diagnostic criteria outlined in the Guidelines for the Diagnosis and Treatment of Primary Osteoporosis for comorbid osteoporosis; (3) Participants must be postmenopausal women aged 50–65 years (50 ≤ age < 65); (4) Participants must not have taken estrogen or medications affecting bone metabolism (e.g., glucocorticoids, antiepileptic drugs, aluminum-containing antacids, proton pump inhibitors, chemotherapy drugs, anticoagulants, or thiazolidinediones) within the past month; (5) Participants must voluntarily enroll in the study, sign an informed consent form, and ensure that the consent process fully adheres to ethical principles.

The exclusion criteria are as follows: (1) Participants with physical disabilities that severely limit mobility or the ability to comply with study procedures, as assessed by clinical investigators; (2) Participants with other autoimmune diseases; (3) Participants with serious heart, liver, or kidney comorbidities; (4) Participants who are pregnant or lactating; (5) Participants who have received immunosuppressive therapy within the last 3 months; (6) Participants who are unwilling or unable to complete follow-up.

To minimize recall bias in fracture reporting, all self-reported fracture events must be confirmed through radiographic evidence (X-ray or CT report); cases without objective imaging confirmation will be excluded from fracture-related analysis.

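### Eligibility admits only women aged 50–64 who already have both diseases, so the aims on prevalence, incidence and risk factors of PMOP-KOA cannot be met in the enrolled cohort

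*Protocol article*

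**What the plan says.** **Aims.** The abstract's Background sets out to "investigate the prevalence, risk factors, and clinical features of PMOP-KOA comorbidity among Beijing residents aged 45–80 years". The abstract's Methods describe two years of screening and follow-up "to investigate the incidence, risk factors, and clinical characteristics of PMOP-KOA". The abstract's Discussion adds: "Data on PMOP-KOA occurrence and associated risk factors over the 2 years follow-up will be available". Section 1 says that the study "aims to investigate the prevalence of PMOP and KOA, explore associated risk factors". Section 3 repeats prevalence and risk factors of the comorbidity as the purpose.

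**Eligibility.** In section 2.4, criterion 2 reads "Participants must meet the diagnostic criteria for KOA, with a KL grade of II or higher (unilateral or bilateral), and simultaneously fulfill" the osteoporosis criteria. Criterion 3 reads "Participants must be postmenopausal women aged 50–65 years (50 ≤ age < 65", that is, 50 to 64 completed years. Section 2 describes "applying predefined inclusion and exclusion criteria to screen participants for an epidemiological investigation", so the criteria govern entry to the survey and not only entry to a later sub-study. The same section says that follow-up is meant to track progression in patients who have PMOP-KOA.

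**Outcomes and size.** Section 2.10 names BMD and clinical information for the cross-sectional phase, and osteoporotic fracture as the key follow-up outcome. Section 2.5 sets the target at 150 participants.

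**The concern.** Prevalence needs a denominator that includes people without the condition. Incidence needs people who are free of it at baseline. Risk factors for having it need non-cases to compare with. Criterion 2 removes all three from the enrolled cohort. The age range in the abstract's aim also differs from the one in criterion 3.

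The study is meant to inform prevention and early identification in the community. A prevalence, an incidence or a comorbidity risk factor reported from this cohort would have no valid basis. It would also be attributed to an age range of which most single years were never eligible.

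**Working it through.** **1. The plan's own figure (section 2.5).** Inputs: d = 0.5, α = 0.05 (two-sided, section 2.11), power 0.80, attrition 15%.
- The exact two-sample t-test calculation gives 63.77 per group, so 64 per group and 2 × 64 = 128 in total, as stated. The normal approximation gives 63 per group, 126 in total.
- Attrition: 128 / (1 − 0.15) = 150.6, so 151; the cruder 128 × 1.15 = 147.2 gives 148. The stated 150 is close to both.
- The other route is five times the number of variables. A result of 150 implies 150 / 5 = 30 variables.

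The figure reproduces. It is sized for a difference between two groups, not for the precision of a prevalence or an incidence. The point here does not depend on it. Note that 150 is the enrolment target, which already contains the attrition allowance.

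**2. Each aim against the eligibility rule.**

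| Aim | What it needs | What criterion 2 leaves |
|---|---|---|
| Prevalence of PMOP-KOA, or of PMOP and KOA separately | Cases / (cases + non-cases) | 150 / 150 = 100% |
| Incidence or occurrence of PMOP-KOA over 2 years | New cases / persons at risk at baseline | 0 persons at risk; undefined |
| Risk factors for the comorbidity | Contrast of cases with non-cases | 0 non-cases; no odds or hazard ratio exists |
| Clinical features of PMOP-KOA | Cases | Estimable |
| TCM-syndrome and gene-expression contrasts | Subgroups within cases | Estimable in principle |
| Fracture incidence and its risk factors | Cases followed for fracture | Estimable in principle |

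The first three rows hold at any sample size and after any loss to follow-up, because they follow from the entry rule alone.

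**3. Age and sex.** Criterion 3 admits ages 50 to 64, which is 15 single years. The range 45 to 80 inclusive has 36. 15 / 36 = 0.417, about 42%. Ages 45–49 and 65–80 are not eligible. This counts calendar ages, not people, and it does not measure bias. Section 3 also lists varying sex ratios as a limitation, although criterion 3 admits only women.

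**The case against.** **A two-stage reading.** The strongest reply is that the study is called a screening, selects communities at random (2.1), mentions a participant screening form (2.8) and plans Taylor linearization (2.11), which is a survey-variance method. On that reading prevalence comes from everyone screened, and a condensed article has left the analysis sets to the full protocol. This has some force for prevalence and for cross-sectional risk factors. It does not remove the contradiction in the text: section 2 applies the criteria at entry to the investigation, and no screened population or denominator is described. It cannot rescue PMOP-KOA incidence, because only existing cases are followed.

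**Stronger readings that the document does not support.**
- A reader might infer that the study can answer none of its questions. That goes too far. The section 2.10 outcomes name neither prevalence nor PMOP-KOA incidence, and all can be studied in cases.
- A reader might infer that the regressions in section 2.11 have a constant outcome. That section does not name PMOP-KOA status as the outcome. Logistic or Cox models fit fracture, and section 3 links fracture incidence with risk factors. The objection applies only to risk factors for the comorbidity itself.
- A reader might infer that screening supplies a ready denominator at no extra cost. Recruitment is by advertisement (2.1), so those screened are volunteers. A woman can fail criterion 2 on DXA alone, or because she lacks the knee pain that Table 1 makes mandatory, without a knee X-ray or the full questionnaire. Analysing only those with complete data would then select on suspicion of disease.

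**Conclusion.** The aims and the eligibility criteria contradict each other and must be reconciled. In the enrolled cohort, PMOP-KOA prevalence is fixed at 100%, the number at risk of new PMOP-KOA is 0, and there are 0 non-cases for a risk-factor comparison. The stated age range exceeds the eligible one by 21 of 36 single years (36 − 15).

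This rests on reading section 2 as written, with the criteria applied at entry to the investigation. If the full protocol defines a screened analysis set, the prevalence and cross-sectional risk-factor part would soften to a need to state that set. The incidence part and the age mismatch would stand.

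The defect is limited to those aims. BMD, clinical description, contrasts within cases, fracture incidence and fracture risk factors are not affected by it. No screening yield can be derived: the nearest figure in section 1, about one in five osteoporosis patients with osteoarthritis, does not concern KOA of KL grade II or higher.

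**What to change.** 1. Delete incidence or occurrence of PMOP-KOA as a follow-up aim. Name osteoporotic fracture incidence, and risk factors for fracture among women with PMOP-KOA, in its place.
2. Restrict the remaining aims to describing women with established PMOP-KOA, including the contrasts between TCM syndromes.
3. State one age range and one sex throughout. The places to edit are the abstract (Background, Methods, Discussion), section 1, criterion 3 if the range changes, and section 3 including its limitations paragraph.
4. Keep a prevalence or comorbidity risk-factor aim only if a screened set is defined in which everyone, irrespective of suspected disease, has the DXA, the knee assessment and the questionnaire. Label the result as an estimate among volunteers recruited by advertisement.

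Items 1 to 3 cost only wording; the downside is narrower claims. Item 4 is not clearly cheap. It may need imaging, questionnaires and consent for people who do not qualify for the cohort. Follow-up runs only to July 2025 (2.9) and parts of section 2.11 are already in the past tense, so collecting such data afterwards may not be possible. Narrowing the aims is the safer choice.
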